## Abstract

**Background:**

Stuttering is a complex speech disorder that affects speech fluency. Recently, it has been shown that noninvasive brain stimulation may be useful to enhance the results of fluency interventions in adults who stutter. Delayed auditory feedback (DAF) is a method to enhance speech fluency in individuals who stutter. Adjunctive interventions are warranted to enhance the efficacy of this intervention.

**Objective:**

Individuals who stutter have pathological activation patterns in the primary and secondary auditory areas. Consequently, in this study, we hypothesize that stimulation of these areas might be promising as an adjunctive method to fluency training via DAF to enhance speech therapy success in individuals with a stutter. We will systematically test this hypothesis in this study.

**Methods:**

This study is designed as a randomized, double-blind, sham-controlled clinical trial. All participants will receive DAF. The intervention group will additionally receive real transcranial direct current stimulation, while the control group will be exposed to sham stimulation. The assignment of the participants to one of these groups will be randomized. Before starting the treatment program, 2 preintervention assessments will be conducted to determine the severity of stuttering. Once these assessments are completed, each subject will participate in 6 intervention sessions. Postintervention assessments will be carried out immediately and 1 week after the last intervention session. Subsequently, to explore the long-term stability of the treatment results, the outcome parameters will be obtained in follow-up assessments 6 weeks after the treatment. The primary outcome measurement—the percentage of stuttered syllables—will be calculated in pre-, post-, and follow-up assessments; the secondary outcomes will be the scores of the following questionnaires: the Stuttering Severity Instrument–Fourth Edition and the Overall Assessment of the Speaker’s Experience of Stuttering.

**Results:**

This protocol was funded in 2019 and approved by the Research Ethics Committee of the Iran University of Medical Sciences in June 2019. Data collection started in October 2019. As of February 2020, we have enrolled 30 participants. We expect data analysis to be completed in April 2020, and results will be published in summer 2020.

**Conclusions:**

We anticipate that this study will show an adjunctive effect of transcranial direct current stimulation, when combined with DAF, on stuttering. This should include not only a reduction in the percentage of stuttered syllables but also improved physical behavior and quality of life in adults who stutter.

**Trial Registration:**

ClinicalTrial.gov NCT03990168; https://clinicaltrials.gov/ct2/show/NCT03990168

**International Registered Report Identifier (IRRID):**

DERR1-10.2196/16646

## Introduction

Stuttering is a complex speech disorder that affects speech fluency, as defined by repetitions, prolongations, and blocks in speech sound [1]. It is prevalent in 1% of the population [2]. Despite advances in the treatment of stuttering, major limitations such as instability of treatment outcomes and lack of long-term results have yet to be addressed [3]. Recently, it has been shown that noninvasive brain stimulation may be useful to enhance the results of fluency interventions in adults who stutter [4]. One of these tools is transcranial direct current stimulation (tDCS), a noninvasive brain stimulation technique that uses a weak, constant current of 1-2 mA that passes through the scalp and results in alterations in cortical excitability and activity [5].

Structural and functional neuroimaging in individuals who stutter show bilateral underactivation of the primary and secondary auditory areas as compared to adults who do not stutter [6]. Delayed auditory feedback (DAF) is a method to enhance speech fluency in individuals who stutter. In this method, alteration of the timing feedback affects speech rate and consequently results in increased fluency [7]. A recent study has shown that in individuals who undergo DAF, enhanced speech fluency is associated with increased activity in the primary and secondary auditory areas of the superior temporal gyrus [8]. DAF is, however, time-consuming, and long-term reductions in stuttering are still restricted [9]. Adjunctive interventions are thus warranted to enhance the efficacy of this intervention. Thus, to increase speech fluency, we will combine DAF as a speech fluency intervention with tDCS applied over the superior temporal gyrus (electrode position T3 of the 10-20 international system) to enhance efficacy of the fluency intervention. Given past evidence that tDCS is capable of inducing plasticity-like changes in cortical functions that can outlast the stimulation period, we anticipate that tDCS will help stabilize intervention-related improvements in speech fluency [10].

In tDCS, electrical current flows between 2 or more electrodes—a positively charged anode and a negatively charged cathode—which are positioned at specified locations on the scalp. The current produced by tDCS results in subtle changes in the resting membrane potential of cortical neurons in the underlying brain tissue [5]. Specifically, with standard protocols, changes under the anode (referred to as anodal stimulation) result in the depolarization of critical neuronal compartments, thus increasing neuronal excitability, while changes under the cathode (cathodal stimulation) result in the hyperpolarization of respective compartments and decrease excitability at the macroscopic level [11]. Neuroplastic effects emerge after some minutes of stimulation, depending on alterations to glutamatergic and GABAergic activities [12,13]. Similar to the acute membrane polarization effects, anodal tDCS and cathodal tDCS result in excitability-enhancing and excitability-reducing plasticity, respectively [10,14,15].

In recent years, studies have shown that tDCS enhances speech fluency in adults who stutter when applied during a fluency intervention [4,16]. Since, in addition to the temporal auditory areas, the frontal cortex shows abnormalities during stuttering, tDCS was applied over the latter area in a recent study [4]. Chesters et al [4] investigated the effect of 5 sessions of anodal tDCS over the left inferior frontal gyrus during a speech fluency intervention on stuttering. Speech fluency significantly improved in the treatment group that received anodal tDCS combined with the fluency intervention in comparison with the respective sham tDCS group. It was concluded that using tDCS simultaneously with fluency training can enhance speech fluency in adults who stutter.

Due to impaired sensory-motor integration, stutterers have pathological activation patterns in the temporal lobe (ie, the primary and secondary auditory areas are underactive while speaking) [6]. Consequently, in this study, we hypothesize that stimulation of these areas might be promising as an adjunctive method to fluency training via DAF, to enhance speech therapy success in individuals with a stutter. We will systematically test this hypothesis in this study.

## Methods

### Overview

This project aims to investigate the effect of adjunctive noninvasive brain stimulation on speech fluency. To this aim, we will recruit 2 groups of participants—an intervention group and a control group. In the intervention group, participants will receive anodal tDCS simultaneously with DAF as a fluency intervention, whereas the participants in the control group will receive sham stimulation during DAF. The population of this study will be adults with a stutter. We hypothesize that anodal tDCS over the temporal target area will improve the efficacy of DAF to enhance speech fluency and will stabilize treatment effects.

### Hypothesis

We hypothesize that the efficacy of the intervention to enhance fluency of speech in individuals with a stutter is improved when combined with anodal tDCS over the superior temporal gyrus, as compared to a sham tDCS control condition.

### Primary Objectives

The primary objective of this proposal is to compare the mean score of the percentage of stuttered syllables (SS%) [17] between the intervention and control groups at 5 time points: 1 week before treatment; immediately before treatment; and immediately, 1 week, and 6 weeks after treatment.

### Secondary Objectives

The secondary objectives are as follows:

Comparison of the mean score of stuttered syllables, duration, physical concomitant behaviors, and total score of the Stuttering Severity Instrument-Fourth Edition (SSI-4) questionnaire [18] between the intervention and control groups 1 week before treatment; immediately before treatment; and immediately, 1 week, and 6 weeks after treatment.Comparison of the means of the general information section, reaction to stuttering section, communication in daily situations section, quality of life section, total impact score, and impact rating of the Overall Assessment of the Speaker’s Experience of Stuttering (OASES) questionnaire [19] between the intervention and control groups 1 week before treatment; immediately before treatment; and immediately, 1 week, and 6 weeks after treatment.

### Efficacy

We expect adjunctive tDCS to enhance the magnitude of the effects of the intervention on our outcome parameters and to enhance the stability of improvements made due to the treatment.

### Safety

There is no anticipated relevant risk associated with the stimulation parameters used in this study [20]. In a systematic review evaluating adverse effects of all published tDCS studies, including studies conducted in vulnerable populations, adverse effects of tDCS such as tingling and itching sensations under the electrodes were mild and disappeared soon after stimulation. No severe adverse effects of tDCS have been documented so far. It thus can be concluded that tDCS within the proposed stimulation parameters is safe [21].

### Study Population

The study population will include adults with moderate-to-severe stuttering who have not received any treatment at least 1 month prior to the intervention. A speech-language pathologist will assess the severity of stuttering in each subject to determine whether he or she can be enrolled. The SSI-4 questionnaire will be used to assess stuttering severity. Inclusion, exclusion, and withdrawal criteria are listed in Textbox 1.

Inclusion, exclusion, and withdrawal criteria.
**Inclusion criteria:**
History of developmental stutteringParticipants diagnosed with moderate-to-severe stutteringRight-handed18 to 50 years of age (adult)Native speaker of FarsiNonsmoker
**Exclusion criteria:**
Stuttering accompanied by other speech or language disordersStuttering treatment within 1 month prior to the interventionHearing lossHistory of neurological or psychiatric disordersHistory of seizuresIntake of any medication that affects brain functions (eg, antidepressants)PregnancyBreastfeedingCranial bone defectsCranial or brain metal implantsSkin lesions
**Withdrawal criteria:**
Request to withdraw from the study at any point during the treatment programSkin damage or major adverse effects of stimulation

### Study Design

This study is designed as a randomized, double-blind, sham-controlled clinical trial. Participants will be randomly allocated to a control or intervention group. All participants will receive DAF during the intervention. The intervention group will additionally receive anodal tDCS, while the control group is exposed to sham tDCS. Data will be collected via questionnaires, voice recordings, and observations at 5 time points (ie, 1 week and immediately before the intervention; and immediately, 1 week, and 6 weeks post intervention). By comparing the outcomes of the respective treatments, we will investigate the efficacy of anodal tDCS combined with DAF in enhancing speech fluency.

Before starting the treatment program, 2 preintervention assessments will be conducted to determine the severity of stuttering. Once these assessments are completed, each subject will participate in 6 intervention sessions. Postintervention assessments will be carried out immediately and 1 week after the last intervention session. Afterward, to explore the long-term stability of the treatment results, the outcome parameters will be obtained in follow-up assessments 6 weeks after the treatment. This single-center trial will be conducted at the Vahdat Neurorehabilitation Clinic in Tehran, Iran.

As previously mentioned, the study will be conducted on adults with moderate-to-severe stuttering; hence, prior to recruitment, the severity of stuttering will be assessed to determine enrollment eligibility. In order to determine the severity of stuttering, an SSI-4 score for each individual will be calculated.

We will obtain two baseline measurements—one at 1 week and the other immediately before the intervention—to guarantee symptom stability. At baseline, the participants will be visited individually, and their voices will be recorded while performing 3 different tasks (ie, oral reading, monologue, and conversation). Based on these data, we will calculate the primary outcome measure (ie, SS%). The voice of the participants will be recorded by a H5 Handy Recorder ZOOM). Two experienced specialist raters will independently count the SS% of all speech samples. In order to determine interrater reliability, Cohen kappa will be calculated. In cases of agreement between the raters (intraclass correlation coefficient=0.8-1), the SS% will be reported. In cases of disagreement (intraclass correlation coefficient <0.8), a third senior rater will evaluate SS%.

During the two baseline sessions, the principal investigator will observe physical behavior, which is required to calculate the SSI-4 score. The final part of the preintervention assessments is the completion of the OASES questionnaire by the participants. After the second baseline assessment, the intervention will start and carry on for 6 consecutive days.

At 3 time points after the last intervention session (ie, immediately, 1 week, and 6 weeks), each subject will undergo postintervention assessments, which will be identical to the preintervention assessments and obtained by the same raters. The trial design and timeline are shown in Figure 1.

After each intervention session, participants will fill out a questionnaire using a 5-point Likert scale (1=very mild, 5=very severe) to report potential side effects of tDCS, including itching, burning, tingling, headache, fatigue, sudden mood change, difficulties in concentration, changes in visual perception, unpleasant somatosensory sensations, unpleasant visual sensations, nausea, drowsiness, persisting feelings of stimulation, and 1 open question for any other adverse effects.

In addition, to ensure successful blinding, participants will be asked to guess the type of treatment they will or had received (ie, anodal tDCS or sham) before and after the intervention.

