#### Performance of Delayed Auditory Feedback

During stimulation, participants of both groups will receive DAF as a fluency treatment. In order to deliver DAF, Audapter, which is a software package for manipulating the acoustic parameters of speech in real time, will be used [24]. This package consists of the core algorithm for real-time manipulation and a MATLAB wrap-around. The real-time signal processing algorithms are coded in C++. The subjects will perform 3 tasks (ie, oral reading, monologue, and conversation) with DAF <60 ms. This 60-ms delay has been shown to be efficient to enhance speech fluency in individuals with a stutter [25].

Although, as outlined above, we do not anticipate major adverse events, the occurrence of skin irritations, itching, tingling, burning, or pain (including headache) will be monitored. After each intervention session, a side effects questionnaire will be filled out by participants. Furthermore, participants will guess if they received anodal or sham stimulation before the intervention, after the first session, and after the intervention period to ensure successful blinding.

Data from the respective questionnaires will be recorded on paper, and recordings of subjects’ voices will be stored electronically. Access to data resources will be restricted to the investigators. Finally, all study documents will be securely maintained for 2 years.

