#### Intended Sample Size

Based on the previous study by Chester et al [4], and using G*Power software [26], 25 subjects per group (50 participants in total) are required to detect a significant difference for a time × group interaction using a two-way mixed model analysis of variance (ANOVA). Time is the within-subject factor (ie, before the intervention and immediately, 1 week, and 6 weeks after the intervention), and group is the between-subject factor (ie, anodal or sham tDCS). The dependent variable is stuttered syllables (SS%). Type I (α) and type II (β) errors are set at .05 and .20, respectively, and the effect size is 0.17.

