#### Other Statistical Analyses

Descriptive statistics will be calculated for demographic and baseline characteristics as well as primary and secondary outcomes for all participants. For every subject, summary statistics including mean, SD, median, minimum, and maximum will be provided for quantitative variables. For qualitative variables, frequency tables will be presented. Group differences of demographic variables will be assessed by Student *t* tests for quantitative variables and chi-square tests for qualitative variables.

In order to evaluate the effect of the treatment, the early and late outcomes (ie, measurements taken immediately, 1 week after treatment, and 6 weeks after treatment) will be examined. Depending on the significance of the ANOVA results, exploratory post hoc Student *t* tests will be conducted to compare conditions. The same procedures will be conducted for the secondary outcome parameters.

Data on tolerability and safety will be analyzed using an independent samples *t* test for common adverse events. Reports of rare side effects will be documented. To confirm successful blinding, a chi-square test will be applied.

Participants may be lost to follow-up for two reasons: (1) they have not completed at least 80% of the treatment (5 out of 6 sessions) and (2) they did not show up for the outcome measurement sessions 1 week or 6 weeks after the intervention. In these cases, intention-to-treat and modified intention-to-treat approaches will be employed. For cases lost to follow-up, efforts will be made to identify the reason, for example, by phone.

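### The side-effect scale has no grade for an absent symptom and the only stated comparison is a t test, so comparing side-effect frequency between arms depends on an unstated rule for blanks

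*Protocol article*

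**What the plan says.** Study Design describes the form completed after each session: "participants will fill out a questionnaire using a 5-point Likert scale (1=very mild, 5=very severe) to report potential side effects of tDCS". It names 13 symptoms and adds "1 open question for any other adverse effects". Both ends of the scale are printed, and neither is an absent category. The article does not say what a participant without a symptom should mark, or how an unmarked item is read.

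The section Performance of Delayed Auditory Feedback states the aim: "the occurrence of skin irritations, itching, tingling, burning, or pain (including headache) will be monitored". The one recording instrument it then names is the side-effects questionnaire.

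Other Statistical Analyses says "Data on tolerability and safety will be analyzed using an independent samples" t test, for common adverse events. It adds: "Reports of rare side effects will be documented". No comparison of proportions is stated for side effects, although a chi-square test is planned for blinding. The variable entered in the t test (item rating, total score or number of events) is not given.

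**The concern.** Occurrence is a yes/no quantity, whereas the printed scale grades severity and starts above zero. A symptom-free participant can mark 1, which mixes absence with a very mild symptom, or leave the item unmarked, which cannot be told apart from a skipped item. The t test on ratings then does one of two things. If absence sits at 1, a difference in frequency is diluted. If blanks are dropped, it compares severity only among those who reported the symptom. That group is formed after randomisation, and the comparison carries no information on how many were affected.

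The split into common and rare events itself needs frequencies. What is at stake is the trial's own tolerability evidence: an unremarkable t test could be read as similar tolerability when one arm had side effects much more often.

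**Working it through.** **Figures in the plan.** The plan gives no figure for side effects. The only input taken from it is the group size: "25 subjects per group (50 participants in total) are required to detect a significant difference for a time × group interaction". As a check on that input, take a repeated-measures within-between interaction with f = 0.17, N = 50, m = 4 time points, α = 0.05, and an assumed correlation of 0.5 with sphericity:

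- λ = f²·N·m/(1 − ρ) = 0.0289 × 50 × 4 / 0.5 = 11.56, with 3 and 144 degrees of freedom.
- Power is 0.814, so 25 per arm reproduces. Nothing below depends on the assumed correlation.

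**Assumptions for the illustration (none is in the document).** One rating per participant per symptom. Severity among those affected is 50/30/15/5/0% on grades 1 to 5, the same in both arms. Mean severity if affected is then 0.5×1 + 0.3×2 + 0.15×3 + 0.05×4 = 1.75.

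**Expected difference in means, true presence 70% versus 30%:**

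- Blanks dropped: 1.75 − 1.75 = 0.
- Absent marked 1: (0.70 − 0.30) × (1.75 − 1) = 0.30.
- Absent coded 0: (0.70 − 0.30) × 1.75 = 0.70.

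**Rejection rates at two-sided 0.05, 25 per arm.** The t tests and chi-square are simulated with 3,000 runs. Fisher is by exact enumeration of the two binomials.

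| Analysis | 70% vs 30% | 60% vs 40% | 50% vs 30% |
|---|---|---|---|
| t test, blanks dropped | 0.05 | 0.05 | 0.06 |
| t test, absent marked 1 | 0.33 | 0.12 | 0.12 |
| t test, absent coded 0 | 0.66 | 0.21 | 0.23 |
| Fisher on presence | 0.78 | 0.24 | 0.23 |
| Chi-square on presence (uncorrected) | 0.86 | 0.32 | 0.33 |

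With blanks dropped, the t test rejects at about its nominal error rate however large the frequency difference.

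**Precision if presence is recorded.** The 95% half-width for a risk difference is 1.96 × √[p₁(1−p₁)/25 + p₀(1−p₀)/25]. At 70% versus 30% this is 1.96 × √0.0168 = 0.254, and at 60% versus 40% it is 1.96 × √0.0192 = 0.272.

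**When frequencies are recoverable.** Suppose a blank does mean absent, and 15 of 25 active and 5 of 25 sham participants mark a symptom with equal severity. Fisher's exact test gives p = 0.009 and the risk difference is 0.60 − 0.20 = 40 points. On the same forms, a t test among reporters compares equal means. So the forms can hold the answer while the stated test does not look for it.

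**The case against.** A reader might infer that side-effect frequency cannot be estimated in this trial. The documents do not support that. If an unmarked item means absent, the proportion affected can be counted in each arm, as the last example shows. The article gives only a short description of the form. A tick-only-if-experienced instruction or a yes/no step may exist in the full form, and its coding may be in an analysis plan that is not shown. The t test's variable is also unstated: a count of reported symptoms would reflect occurrence to some extent. These points stand, and they limit the claim to what is printed. They do not remove it, because the article prints both anchors and names the test, and these stated choices fit poorly with the stated aim of monitoring occurrence. A later analysis plan cannot restore presence or absence if the form did not capture it.

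Three further arguments carry less weight:

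- **Items.** Skin irritation and general pain are named as monitored but are not among the 13 listed symptoms. The list is introduced as non-exhaustive, headache and burning are on it, and the open question can catch the rest. Aligning the two lists is tidying.
- **Blinding.** Side-effect frequency would help interpret the arm guesses, but the guesses are collected and tested directly, so blinding does not hinge on this form.
- **t test versus rank test.** For a five-point rating this choice is secondary. The main issue is which quantity is compared.

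**Conclusion.** The point holds in a limited form. As printed, the scale does not define absence and the only named between-arm analysis does not compare the proportion affected. Recovery of occurrence rests on an unstated rule for blanks.

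In the illustration at 70% versus 30%, the t test on the printed scale misses the difference about two times in three if absence is marked 1, and almost always if blanks are dropped. These sizes rest on assumed rates, equal severity in both arms, and the t test being applied to item ratings. With smaller differences every analysis is weak at 25 per arm. The gain there is an estimate of the right quantity with its interval, not much extra power.

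The matter affects tolerability reporting only. It leaves the percentage of stuttered syllables and the sample size untouched. It is worth correcting but is not a bar to the trial.

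**What to change.** - Add an explicit grade 0 (not present) to every item for participants still to be treated, and add skin irritation and pain so that the form matches the monitoring statement.
- Make the main tolerability comparison the per-arm proportion of participants with each side effect in any of the six sessions, reported as a risk difference with a confidence interval and Fisher's exact test. Support it with an ordinal comparison of worst severity, counting absence as the lowest level.
- For completed forms, keep blanks distinct from 1s in the data set. Report results under both readings: every marked 1 as a very mild symptom with blanks absent, and marked 1s as possibly absent.

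**Cost.** One revised form and a few lines of analysis text. The article reports 30 enrolled by February 2020, so at most 50 − 30 = 20 participants of the planned total could have started on a revised form after that date. The drawback is a mixed data set: earlier forms use the old scale and may not be fully recoverable, so results should be shown by form version as well as combined.
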